**7. Safety Evaluation**

The investigator is responsible for monitoring the safety of all enrolled subjects and recording any adverse events (AEs) and serious adverse events (SAEs). AEs monitoring began after the first patient enrollment and was monitored continuously until the last follow-up.

7.1 Safety Observation Indicators

- Medical History Inquiry: Comprehensive recording of clinical characteristics and causes of patient complaints.

- Physical Examination: Height, weight, vital signs (including ECOG score), and examination of various organs.

- Laboratory Examination Indicators: Complete blood count, biochemical routine, urinalysis, stool routine, EBV-DNA, coagulation function, thyroid function, six items of cardiac function, NYHA cardiac function classification, and 12-lead electrocardiogram.

7.2 Definition of Adverse Events (AEs)

Treatment-related AEs, including hematological and non-hematological AEs, were defined as those that occurred from the start of treatment. For pre-existing abnormalities in physical or laboratory examinations, an increase in severity after treatment was also considered as an AE. The investigator should record all AEs in detail, including descriptions and related symptoms, time of occurrence, severity, duration, measures taken, and outcomes.

7.2.1 Criteria for Determining the Severity of AEs

The severity of AEs was graded according to the NCI-CTCAE v5.0 criteria. For adverse reactions not listed in the table, refer to the following standards:

- Grade I: Mild, no clinical symptoms or mild clinical symptoms; only clinical or laboratory examination abnormalities; no treatment required.

- Grade II: Moderate, minimal, local, or noninvasive treatment required; age-appropriate tools indicate limited daily activities, including cooking, shopping, using the phone, and handling money.

- Grade III: Severe disease or significant clinical symptoms but not life-threatening; requires hospitalization or prolongs hospitalization; causes disability; limited self-care daily activities (e.g., bathing, dressing, eating, using the toilet, taking medication, not bedridden).

- Grade IV: Life-threatening, requiring emergency treatment.

- Grade V: Death due to AE.

7.2.2 Criteria for Determining the Relationship Between AEs and Study Drug

All AEs must be reported in clinical reports, and any discomfort or abnormal changes in objective laboratory indicators during the trial must be recorded accurately, indicating the severity, duration, treatment measures, and outcomes. Clinicians should use a five-category method ("definitely related," "probably related," "possibly unrelated," "definitely unrelated," and "unable to determine") to comprehensively judge the relationship between AE and the study drug. "Definitely related," "probably related," and "unable to determine" are classified as drug adverse reactions. The incidence of AEs is calculated as the sum of these three categories as the numerator and the total number of subjects evaluated for safety as the denominator.

| **Category** | **Criteria** |
| --- | --- |
| Definitely related | The event occurs in a reasonable sequence after drug administration, matches the known reaction type of the suspected drug, improves after discontinuation, and recurs after re-administration. |
| Probably related | The event occurs in a reasonable sequence after drug administration but does not match the known reaction type of the suspected drug; the patient's clinical status or other treatments may also cause the event. |
| Possibly unrelated | The event does not occur in a reasonable sequence after drug administration, does not match the known reaction type of the suspected drug, and the patient's clinical status or other treatments may cause the event. |
| Definitely unrelated | The event does not occur in a reasonable sequence after drug administration, does not match the known reaction type of the suspected drug, the patient's clinical status or other treatments may cause the event, and the event disappears after discontinuing other treatments or improving the disease and reappears after reintroducing other treatments. |
| Unable to determine | The event's occurrence and timing have no clear relationship with drug administration, similar to the drug reaction type, and other concurrent medications may also cause the event. |

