| **Safety measures** | Treatment-related AEs, including hematological and non-hematological AEs, were defined as those that occurred from the start of treatment. Early deaths were defined as deaths occurring within 30 days of treatment with this regimen. The severity of AEs was assessed following the Common Terminology Criteria for Adverse Events (CTCAE, v5.0) of National Cancer Institute during treatment. |
| **Statistical analysis** | Clinical characteristics of patients were summarized by utilizing frequencies (%) for categorical variables and medians (range) for continuous variables. Fisher’s exact test was used to compare the associations for categorical variables versus categorical variables. Wilcoxon rank sum test was employed to compare categorical variables versus continuous variables. False discovery rate (FDR) corrected by Benjamini-Hochberg approach was applied to adjust the p value for multiple testing unless otherwise specified. Kaplan–Meier survival curves were utilized to evaluate the probabilities of OS and EFS. Log-rank test was performed to compare the survival curves. Asterisks define significance levels. All statistical tests were two-sided unless otherwise specified. Statistical analyses were carried out using R (v4.1.0) packages. |
| **Enrollment time** | 12 January 2015 to 12 February 2022 |
| **Final follow-up** | 31 March 2023 |

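### The rate called AE incidence is a causality-filtered adverse-reaction rate with no counting unit; it conflicts with the timing-only definition of treatment-related AEs and rests on a causality table with a gap

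*Protocol*

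**What the plan says.** The Synopsis (Study endpoints) lists treatment-related AEs as a secondary endpoint. Section 7.2 defines them by timing alone: "Treatment-related AEs, including hematological and non-hematological AEs, were defined as those that occurred from the start of treatment". The Safety measures row of the Synopsis agrees: they "were defined as those that occurred from the start of treatment".

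Section 7.2.2 takes a different route. Clinicians use five categories "to comprehensively judge the relationship between AE and the study drug". Three of these, *definitely related*, *probably related* and *unable to determine*, "are classified as drug adverse reactions". The next sentence gives the rate: "The incidence of AEs is calculated as the sum of these three categories as the numerator", with "the total number of subjects evaluated for safety as the denominator". The same section opens with the requirement that "All AEs must be reported in clinical reports".

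The table in Section 7.2.2 sets the criteria. *Definitely related* needs reasonable timing, a known reaction type, improvement on stopping and recurrence on re-administration. *Probably related* reads: "The event occurs in a reasonable sequence after drug administration but does not match the known reaction type of the suspected drug", and adds that another cause is possible.

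**The concern.** Three faults in the stated rules bear on the safety endpoint.

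- **Two meanings of relatedness.** An event after the start of treatment that is judged *definitely unrelated* is treatment-related under Section 7.2 and outside the rate under Section 7.2.2.
- **A mislabelled rate without a unit.** A subset that the protocol itself calls adverse reactions is reported as the incidence of AEs. Causality ratings attach to events, the denominator is subjects, and no rule counts a subject once.
- **A gap in the causality table.** A well-timed event of known type that does not recur on re-administration meets no row.

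The trial is open-label with a single arm. All-causality incidence is then the safety result least dependent on judgement, and it is the one that the name AE incidence should denote. The relatedness scale is also used elsewhere: Section 7.3.8 requires follow-up of drug-related AEs, and Section 7.3.5 limits SAE reporting beyond 90 days to events suspected to be related.

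**Working it through.** The protocol gives no AE rate, so there is no figure to reproduce. The check is a comparison of definitions, an illustration of the rate with assumed counts, and an enumeration of the table.

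**1. Same event, two definitions.** Take an event after the first dose that is rated *possibly unrelated* or *definitely unrelated*. Under Section 7.2 and the Synopsis it counts, because only timing matters. Under Section 7.2.2 it does not, because neither category is among the three summed. The two numerators differ by all events with these ratings.

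**2. The rate as written.** Incidence = (n_definitely + n_probably + n_unable) / N. Section 15 gives 51 enrolled; N = 51 is used here for illustration. The category counts are assumptions, read as subjects with at least one event in that category. The proportion of subjects with any such event lies between max(n)/N, when the categories overlap fully, and min(N, sum)/N, when they overlap as little as possible.

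| Assumed counts | Rate as written | Subjects with at least one such event |
|---|---|---|
| 20 / 15 / 10 | 45/51 = 88.2% | 20/51 = 39.2% to 45/51 = 88.2% |
| 30 / 20 / 10 | 60/51 = 117.6% | 30/51 = 58.8% to 100% |
| 40 / 30 / 20 | 90/51 = 176.5% | 40/51 = 78.4% to 100% |

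If the numerator is events, the sum can also exceed the number of subjects. If it is tabulated per AE term with one rating per subject, the categories are exclusive and each subject counts once. The text does not say which is meant.

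**3. The causality table.**

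| Category | Reasonable timing | Known reaction type | Further conditions | In the rate |
|---|---|---|---|---|
| Definitely related | yes | yes | improves on stopping and recurs on re-administration | yes |
| Probably related | yes | no | another cause possible | yes |
| Possibly unrelated | no | no | another cause possible | no |
| Definitely unrelated | no | no | another cause possible, and the event follows withdrawal and return of other treatment | no |
| Unable to determine | no clear relationship | similar | other concurrent drugs possible | yes |

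Code each event yes or no on timing, known type, improvement on stopping, recurrence and alternative cause: 2^5 = 32 combinations. Treat unclear timing as not reasonable, and merge the two unrelated rows.

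- Reasonable timing, known type: 8 combinations. Only the 2 with both improvement and recurrence fit a row, so 6 have none.
- Each of the other three timing-by-type groups: 8 combinations. The 4 with an alternative cause fit and 4 do not.
- Total without a row: 6 + 4 + 4 + 4 = 18 of 32.

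The group of 8 matters most, since it describes an expected drug reaction. The ordering is also odd: an event of known type with unclear timing can be counted as *unable to determine*, while one with good timing and no recurrence has no row.

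**The case against.** Much can be said for the protocol, and most of it limits the point without removing it.

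- **A reader might infer that all-causality data are lost.** They are not. Section 7.2 requires all AEs to be recorded in detail, Section 7.2.2 requires all to be reported, and Section 2.2.2 lists safety as haematological and non-haematological AEs without a causality filter. The sentence on incidence is most naturally a mislabelled adverse-reaction rate. The label and the conflict remain.
- **A reader might infer that the rate must exceed 100%.** The unit is unstated, so this is possible and not certain. The percentages above rest on assumed counts.
- **A reader might infer that the best-known toxicities cannot be classified.** Section 5.2 gives two chemotherapy cycles followed by maintenance. A cytopenia that recovers and returns in the next cycle can meet *definitely related*. The gap concerns events seen once, or first seen in the last cycle.
- **A reader might infer that the cord blood safety conclusion is unreliable.** Section 7.3.6 makes GVHD of any grade and infusion reactions of grade 3 or higher reportable without a causality condition, and Section 7.3.7 adds SAE reporting for grade 3 or 4 infusion reactions. These harms do not depend on the table to be captured.
- **The rows need not be a strict key.** Section 7.2.2 asks for a comprehensive judgement. A clinician who meets the gap may choose *definitely*, *probably* or *unable to determine*, all of which are counted, and the rate would then not change. But the written criteria are then not being applied, and ratings may differ between clinicians.

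**Conclusion.** The point holds as an error in the stated rules. Treatment-related AEs are defined by timing in the Synopsis and Section 7.2, while Section 7.2.2 filters by causality and gives the filtered rate the name of AE incidence. Followed literally, that rate omits every event rated unrelated and may count a subject more than once. The causality table leaves 6 of the 8 combinations with reasonable timing and known type without a row.

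The size of the effect on the reported rates cannot be stated, because the protocol holds no AE counts. The 6 of 8 and 18 of 32 rest on a literal reading of the rows; the percentages above 100% rest on assumed counts and on summing without removing overlap. The documents do not support a claim that AE data are missing or that the main cord blood harms go undetected. The primary endpoint, OS, is not affected. The correction should be made before any AE rate is relied on.

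**What to change.** 1. **Synopsis (Study endpoints, Safety measures) and Section 7.2:** call events from the start of treatment *treatment-emergent AEs*, regardless of cause. All three places must change, or the conflict remains.
2. **Section 7.2.2, rate:** define AE incidence as subjects with at least one treatment-emergent AE divided by the number in the safety analysis set, by term and worst grade. Report adverse reactions as a separate, named subset, each subject counted once.
3. **Section 7.2.2, table:** define *probably related* as reasonable timing and a known reaction type, without requiring re-administration. Move its current text to a new *possibly related* row, and state that this row counts as an adverse reaction, as that text does now.

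The cost is wording and re-tabulation, and reported AE rates may rise. The all-causality table needs no re-rating. Follow-up ended on 31 March 2023, so any re-rating of causality for the subset would be retrospective and should be disclosed as such.

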7.3 Serious Adverse Events (SAEs)

7.3.1 Definition of SAEs

SAEs refer to medical events during a clinical trial that require hospitalization or prolong hospitalization, cause disability, affect work ability, are life-threatening or result in death, or cause congenital malformations. This includes the following unexpected medical events:

- Events leading to death.

- Life-threatening events (defined as events where the subject is at risk of death at the time of occurrence).

- Events causing significant or permanent physical disability or organ function impairment.

- Events potentially leading to permanent or serious disability/loss of work ability.

- Carcinogenic, teratogenic, or birth defects.

- Other significant medical events requiring intervention to prevent permanent damage or injury.

7.3.2 Disease Progression

Disease progression is defined as the worsening of clinical symptoms/signs of the disease for the study drug, the emergence of new metastases relative to the primary malignance, or the progression of existing lesions. Symptoms and signs caused by disease progression leading to death, life-threatening conditions, hospitalization, or extended hospitalization, causing permanent or serious disability/loss of work ability, or birth defects are not reported as SAEs. Death due to disease progression symptoms and signs should be reported as SAEs.

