5.5 Follow-up Evaluation

Schedules:

- Post-UCB treatment on days 14, 30, and 60.

- Before each chemotherapy session and before and after each maintenance treatment during the treatment period.

- After the end of treatment, follow-up assessments were performed monthly in the first year, and every three months thereafter.

Testing Items:

- Bone marrow aspiration smear, MRD, bone marrow chimerism detection.

- Chromosome testing was required after consolidation and maintenance therapy.

- If there was any disease recurrence detected by bone marrow cytology at any time during the treatment, the treatment will be deemed ineffective. Then the patient will be withdrawn from this study and enter the trials for relapsed and refractory AML treatment.

- If bone marrow chimerism > 30% at any time during treatment, donor engraftment will be considered, and the patient will be withdrawn from the clinical trial and receive anti-rejection treatment.

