7.4 Common Adverse Reactions of Decitabine

1) Hematologic Toxicity:

- Neutropenia (low neutrophil count)

- Thrombocytopenia (low platelet count)

- Anemia (low red blood cell count)

- Leukopenia (low white blood cell count)

- Febrile neutropenia (fever with low neutrophil count)

2) Infections:

- Increased susceptibility to infections, including pneumonia, sepsis, and upper respiratory infections

3) Gastrointestinal:

- Nausea

- Vomiting

- Diarrhea

- Constipation

- Abdominal pain

4) General:

- Fatigue

- Fever

- Weakness

- Edema (swelling)

5) Hepatic:

- Elevated liver enzymes (ALT, AST)

- Hyperbilirubinemia (elevated bilirubin levels)

6) Cardiovascular:

- Hypotension (low blood pressure)

7) Dermatologic:

- Rash

- Petechiae (small red or purple spots on the body)

8) Respiratory:

- Cough

- Dyspnea (difficulty breathing)

9) Musculoskeletal:

- Arthralgia (joint pain)

- Myalgia (muscle pain)

10) Renal:

- Elevated serum creatinine

11) Neurologic:

- Headache

- Dizziness

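### The SAE exemption for disease progression (7.3.2) uses a solid-tumour, sign-based definition not tied to the marrow criterion in 5.5, and gives opposite instructions on fatal progression

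*Protocol*

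**What the plan says.** Protocol section 7.3.2 has three sentences.

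- The first is the definition: "Disease progression is defined as the worsening of clinical symptoms/signs of the disease for the study drug, the emergence of new metastases", to which it adds growth of lesions already present. It names no marrow, blast-count or blood criterion.
- The second is the exemption. It begins "Symptoms and signs caused by disease progression leading to death, life-threatening conditions, hospitalization, or extended hospitalization", continues through disability, and ends "or birth defects are not reported as SAEs".
- The third reads: "Death due to disease progression symptoms and signs should be reported as SAEs".

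Section 5.5 has a separate, objective rule for recurrence, which begins "If there was any disease recurrence detected by bone marrow cytology at any time during the treatment" and leads to withdrawal from the study. Section 7.3.2 does not refer to it.

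Inclusion criterion 7 (section 4.1) requires documented complete remission at entry. Section 7.4 lists cytopenias, febrile neutropenia and fever as decitabine reactions, together with "Increased susceptibility to infections, including pneumonia, sepsis, and upper respiratory infections". Section 7.5 lists cytopenias, fever and infection risk for cytarabine.

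**The concern.** An exemption of this kind works only if progression can be told apart from toxicity. Here the definition was evidently written for solid tumours. In AML patients in remission, its metastasis and lesion criteria have little or nothing to act on, so the exemption rests on clinical signs. Several signs that an investigator might read as returning leukaemia are the same ones that the protocol lists as drug reactions.

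Two things are at stake. First, a life-threatening or hospitalised infection during chemotherapy cytopenia could be put down to progression with no evidence of relapse, and so not be sent as an SAE to the Ethics Committee, the only recipient named in 7.3.5. Second, whether a fatal progression is an SAE depends on which of two adjacent sentences the investigator follows. Safety is part of the study objective (2.1) and a secondary endpoint (2.2.2), so SAE counts from this trial should follow one rule.

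**Working it through.** No arithmetic applies, because the point concerns the wording of a reporting rule. The check sets the sections side by side.

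1. **Does the definition fit the population?** Section 7.3.2 offers three routes to progression: worsening symptoms or signs, new metastases, and progressing lesions. Section 4.1 admits only AML patients in documented remission. The second and third routes are close to empty for them. The first remains, and 7.3.2 sets no laboratory or marrow threshold for it.

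2. **Do signs separate leukaemia from toxicity?** Sections 7.4 and 7.5 list neutropenia, thrombocytopenia, anaemia, fever and infection as reactions to the study drugs. That active AML can produce similar findings is general clinical knowledge and is not stated in the protocol. On that assumption, signs alone do not separate the two.

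3. **Is better evidence already collected?** Yes. Section 5.5 schedules marrow smear and MRD on days 14, 30 and 60 after cord blood, before each chemotherapy session, before and after each maintenance treatment, and then monthly for a year and every three months. It also defines recurrence by marrow cytology. The exemption uses none of this.

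4. **Does another section catch a misattributed non-fatal event?**
   - As an SAE, not reliably. Section 7.3.4 makes AEs that lead to hospitalisation SAEs, while 7.3.2 exempts hospitalisation caused by progression; nothing says which prevails. General infection and bleeding are not among the events of special interest in 7.3.6.
   - As an AE, yes. Section 7 requires AEs to be monitored until last follow-up, 7.2 requires all AEs to be recorded in detail, and 7.2.2 requires all AEs to be reported. The exemption removes SAE reporting only.

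5. **What happens to a fatal progression?**

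| Place | Instruction |
| --- | --- |
| 7.3.2, second sentence | Symptoms and signs of progression with a fatal outcome: not an SAE |
| 7.3.2, third sentence | Death from symptoms and signs of progression: SAE |
| 7.3.1 | Events that lead to death: SAE, with no exception for progression |
| 7.3.3 | Death after study treatment but within the SAE reporting period: report promptly, with no exception for progression |

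Three statements require reporting and one exempts. The exemption of fatal cases is the outlier.

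**The case against.** The strongest case on the other side has four parts.

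- **The exemption is narrow by its own terms.** It covers only symptoms and signs caused by progression, so a drug-induced infection is outside it. The marrow schedule in 5.5 also means that remission status would often be known at about the time of toxicity. This limits how often misattribution is likely, but does not close the gap: 7.3.2 does not require the investigator to use that evidence.
- **The sentences on death can be reconciled.** One may read them as exempting the symptoms and reporting the death. That reading is workable, but the text does not state it, and both sentences cover the same fatal cases.
- **Other safeguards exist.** AE recording continues. Section 7.2.2 counts events of undeterminable relationship as drug reactions, which leans towards attribution to treatment. The safety endpoint in 2.2.2 is AEs graded by CTCAE, not an SAE count. All of this stands and limits the consequence to SAE reports.
- **GVHD is already covered.** Section 7.3.6 makes any grade notifiable within 24 hours, so no added provision is needed.

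A reader might go further and infer that deaths caused by the regimen go unreported. The documents do not support that. Sections 7.3.1, 7.3.3 and the last sentence of 7.3.2 call for reporting, the synopsis defines early deaths within 30 days as a safety measure, and overall survival counts death from any cause. The fault for deaths is conflicting instructions, not a clear exemption.

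**Conclusion.** The point holds as a defect in the SAE reporting rule. The definition in 7.3.2 does not fit AML patients in remission and is detached from the marrow criterion in 5.5. As written, it could leave serious non-fatal toxicity out of SAE reports while the event is still recorded as an AE. Its instructions on fatal progression contradict each other and, in the exempting sentence, also contradict 7.3.1 and 7.3.3.

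No event count can be attached. The protocol gives no SAE numbers and no count of events coded as progression. It is tempting to size the problem from the planning survival rates (3.2) or the background relapse rate (section 1). Those figures would count mainly true relapses and all-cause deaths, and they ignore that SAE reporting generally ends 90 days after the last administration (7.3.5). They do not measure toxicity misread as progression.

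A reader might also infer a demonstrated bias that makes the regimen look safer. Misuse of the exemption could only remove events from the SAE count, but nothing shows that any event was misattributed, and the AE-based safety endpoint does not depend on this section. The conclusion assumes only that signs of AML overlap with the listed toxicities. No efficacy endpoint, analysis set or test is affected.

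**What to change.** 1. In 7.3.2, replace the sign, metastasis and lesion definition with recurrence shown by bone marrow cytology, as already used in 5.5, and limit the exemption to events caused by recurrence so established.
2. Remove the fatal outcome from the exempted list, so that 7.3.2 agrees with its own last sentence and with 7.3.1 and 7.3.3.
3. Section 15 gives last follow-up as 31 March 2023, so rewording alone will not change reports already made. Before SAE counts are reported, check every serious event coded as progression against the patient's marrow dates, and state in the report which rule the counts follow.

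The change concerns only what is reported as an SAE; it does not touch treatment or withdrawal rules. The cost is rewording one section and a small record check at one centre with 51 enrolled patients, using marrow results that the schedule in 5.5 already calls for. The downside is a slightly higher SAE count if any events are reclassified.
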